# The NEtherlands Cervical Kinematics (NECK) Trial. Cost-effectiveness of anterior cervical discectomy with or without interbody fusion and arthroplasty in the treatment of cervical disc herniation; a double-blind randomised multicenter study

**DOI:** 10.1186/1471-2474-11-122

**Published:** 2010-06-16

## Abstract

**Background:**

Patients with cervical radicular syndrome due to disc herniation refractory to conservative treatment are offered surgical treatment. Anterior cervical discectomy is the standard procedure, often in combination with interbody fusion. Accelerated adjacent disc degeneration is a known entity on the long term. Recently, cervical disc prostheses are developed to maintain motion and possibly reduce the incidence of adjacent disc degeneration. A comparative cost-effectiveness study focused on adjacent segment degeneration and functional outcome has not been performed yet. We present the design of the NECK trial, a randomised study on cost-effectiveness of anterior cervical discectomy with or without interbody fusion and arthroplasty in patients with cervical disc herniation.

**Methods/Design:**

Patients (age 18-65 years) presenting with radicular signs due to single level cervical disc herniation lasting more than 8 weeks are included. Patients will be randomised into 3 groups: anterior discectomy only, anterior discectomy with interbody fusion, and anterior discectomy with disc prosthesis. The primary outcome measure is symptomatic adjacent disc degeneration at 2 and 5 years after surgery. Other outcome parameters will be the Neck Disability Index, perceived recovery, arm and neck pain, complications, re-operations, quality of life, job satisfaction, anxiety and depression assessment, medical consumption, absenteeism, and costs. The study is a randomised prospective multicenter trial, in which 3 surgical techniques are compared in a parallel group design. Patients and research nurses will be kept blinded of the allocated treatment for 2 years. The follow-up period is 5 years.

**Discussion:**

Currently, anterior cervical discectomy with fusion is the golden standard in the surgical treatment of cervical disc herniation. Whether additional interbody fusion or disc prothesis is necessary and cost-effective will be determined by this trial.

**Trial Registration:**

Netherlands Trial Register NTR1289

## Background

Anterior cervical discectomy (ACD) is the basic surgical treatment of patients with radicular pain caused by cervical disc herniation. In 1958, Cloward, Smith and Robinson first described anterior cervical decompression with the use of autologous iliac crest interbody graft (ACDF)[1]. Shortly after, Hirsch debated the necessity of interbody fusion[2]. The results of various prospective randomised trials suggest that interbody fusion may not be necessary in all cases, although due to methodological flaws no solid conclusions can be drawn[3-9]. The Cochrane Review even mentioned advantages of anterior discectomy only (e.g. costs, operation time and return to work)[10].

At present, ACDF is defined as the golden standard for cervical disc herniation to maintain disc height, cervical alignment, and promote bony fusion. However, arthrodesis of a motion segment will lead to increased degenerative changes at the adjacent level. The concept of accelerated adjacent disc degeneration (AADD) is widely discussed and Hilibrand et al. reported an annual incidence of 2.9% symptomatic AADD after fusion[11].

The main rationale of artificial disc replacement is motion preservation with subsequent prevention of adjacent disc degeneration. Various prospective randomised trials have shown that cervical disc prosthesis is a safe and reliable alternative to cervical fusion[12-17]. However, limited studies have focused on symptomatic AADD and the follow-up period is short[18,19].

In the NEtherlands Cervical Kinematics (NECK) trial, we will randomly and blindly compare anterior cervical discectomy *sec *(ACD), with anterior discectomy with fusion (ACDF), and anterior discectomy with disc prosthesis (ACDP) in 3 treatment groups. We hypothesise a difference in symptomatic adjacent level disease in favour of disc prosthesis and better clinical outcome and self-assessment measured by the Neck Disability Index (NDI). As such we will evaluate the clinical appropriateness and superiority of disc prosthesis on one hand, cervical fusion on the other hand, and compare this to discectomy without any implant. Moreover, we will identify possible subgroups of patients who will substantially benefit from one of the allocated surgical treatments.

## Methods/Design

We designed an observer and patient blinded randomised cost-effectiveness trial in the treatment of cervical disc herniation in which three surgical techniques are compared in a parallel group design. Adjacent level disease will be used as primary outcome measure and NDI as secondary outcome. As such we will evaluate the clinical appropriateness and superiority of disc prosthesis on one hand, cervical fusion on the other hand, and compare this to discectomy without any implant. The follow-up period will last 5 years.

In order to collect enough patients, a multicenter design is necessary. The clinical centers that are planned to recruit patients into the NECK trial are: Medical Center Haaglanden, The Hague; Leiden University Medical Center; University Medical Center Groningen; Medical Center Alkmaar; and University Medical Center Maastricht. The protocol was approved by the ethics committee/IRB in each participating hospital.

The primary question of the NECK trial is whether ACDP has a lower incidence of symptomatic adjacent disc degeneration compared to ACD and ACDF. Symptomatic adjacent level disease is defined as development of new symptoms (i.e. neck pain, radiculopathy, or myelopathy) referable to a motion segment adjacent to the site of the previous anterior surgery. In addition, we want to identify certain subgroups that may benefit more of one of the allocated treatments.

### Patients

All patients between 18 and 65 years with monoradicular symptoms in one or both arms lasting more than 8 weeks are eligible for the NECK trial. MRI must confirm cervical disc herniation and/or osteophyte in accordance with clinical symptoms. Additional inclusion and exclusion criteria are listed in Table 1.

**Table 1 T1:** Selection criteria for trial eligibility.

**Inclusion criteria**
Age 18 - 65 years
Radicular signs and symptoms in one or both arms
At least 8 weeks prior conservative treatment
Radiographic diagnosis of cervical disc herniation and/or osteophyte at 1 level (C3-C4 to C7-T1) in accordance with clinical signs and symptoms
Informed consent
**Exclusion criteria**
Previous cervical surgery (either anterior or posterior)
No motion of the index level on dynamic studies
Increased antero-posterior motion of the index level on dynamic studies (>3 mm)
Involved disc level fused or very narrow (central <3 mm)
Severe segmental kyphosis of involved disc level (>3 degrees)
Neck pain only
Symptoms and signs of chronic myelopathy
Infection, bone disease, neoplasm or trauma of the cervical spine
Spinal anomaly (Klippel-Feil, Bechterew, OPLL)
Severe mental or psychiatric disorder
Inadequate Dutch language
Planned (e)migration abroad in the year after inclusion

Patients are referred by a neurologist with MRI of the cervical spine. During the first visit to the neurosurgical outpatient clinic, the patient's history and a standard neurological examination will be documented. Conform our selection criteria, the neurosurgeon decides whether a patient is eligible for the NECK trial. The study will be explained to the patient and, in case of a positive reaction, an appointment is made with one of the research nurses. Because the patient needs some time to consider participation, the first visit to the research nurse is planned after at least 2 days. After informed consent, the questionnaires, outcome measures, and baseline variables are recorded.

### Randomisation procedure

Patients will be randomly allocated to ACD, ACDF, or ACDP. Randomisation will take place on the operating room within 6 weeks after the first visit to the research nurse. A randomisation list is prepared for every participating hospital-nurse combination. Variable sized blocks of random numbers are formed to ensure equal distribution of the randomisation treatments over hospitals and research nurses. The data manager, who is not involved in the selection and allocation of patients, will prepare coded, sealed envelopes containing the treatment allocation. In the operating room, after induction of anaesthesia, the surgeon will open the envelope and the allocated treatment will be performed. Patients and research nurses will be kept blinded for the allocated treatment for 2 years.

### Intervention

Patients will be randomised into anterior discectomy *sec *(group A), anterior discectomy with interbody fusion (group B), and anterior discectomy with arthroplasty (group C). The participating surgeons have large experience in all three techniques. A standardized Case Record Form (CRF) will register the surgeon's findings and this CRF, together with the randomisation envelope, will be returned to the data center in a sealed envelope.

### (A) Anterior cervical discectomy (ACD)

All patients will be positioned supine with their neck in neutral position or slightly extended under general anaesthesia. The affected cervical disc level will be verified with fluoroscopy. A small transverse incision will be made either on the right side or the left side depending on the surgeon's preference. Medial to the carotic sheath, the pre-vertebral space will be opened and the anterior cervical spine will be exposed. Two distraction pins and the Caspar spreader will be placed in the affected segment. A standard anterior discectomy with the aid of microscope or loupe/headlight magnification (depending on the surgeon's preference) will be performed in all cases. The posterior longitudinal ligament will be opened and the nerve root and dura will be decompressed adequately. If required a vacuum drain will be placed and the wound will be closed in layers.

### (B) Anterior cervical discectomy with interbody fusion (ACDF)

Once the anterior discectomy has been performed, an interbody cage filled with bone substitute will be placed within the intervertebral space under fluoroscopic guidance. The type of cage depends on the surgeon's preference and daily practice. To prevent pain from the iliac crest, no autologous bone will be used.

### (C) Anterior cervical discectomy with disc prosthesis (ACDP)

The device used in the present trial is the Activ-C Flat artificial disc (B. Braun Aesculap, Germany)[20]. After the standard anterior discectomy is performed, the implant size will be determined and the endplates will be prepared for proper fitting of the prosthesis. The device will be inserted under slight distraction and fluoroscopic guidance. Whenever, for surgical-technical reasons, it is not possible to implant the disc prosthesis, an interbody fusion will be performed. Whenever this is impossible as well, only discectomy will be performed.

All patients will be encouraged to mobilise as soon as possible without a collar. Hospital admission will be 1-3 days, depending on the usual care of the participating hospital. Patients are stimulated to resume home activities and work as soon as possible.

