### 3) Complications

A systematic assessment of complications (including wound infection, deep venous thrombosis, urine tract infection, haematoma, progressive neurological deficit, dysphagia, and hoarseness) will be carried out by the surgeon and research nurse. Surgeons will also document perioperative complications like cerebrospinal fluid leakage, vascular injury, nerve root damage, and malposition of the implant.

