### 4) Radiographic evaluation

Besides adjacent disc degeneration (primary outcome measure), we will also evaluate the cervical curvature, segmental motion, displacement or migration of the implant, and heterotopic ossification using the classification of McAfee[38].

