### Data Analysis

The data will be analysed according to the stopping rules, i.e. after approximately 1.8, 2.6 and 3.2 years under H0 and 2.2, 3.2 and 4.2 years under H1. The actual analysis times depend on the number of events observed (15, 30 and 45). This establishes an answer to the main objectives in terms of the comparison of ADCF to ADCP. Long-term analyses of all results will be conducted irrespective of an early achievement of futility or efficacy establishing a comparison at 52, 104, 156, 208 and 260 weeks. However, these analyses will be performed after the final analysis of the trial has reached the conclusion of efficacy or futility. For all analyses, assessments performed at the first outpatient visit will be taken as baseline. Baseline comparability will be analysed by descriptive statistics to determine whether randomisation was successful. Baseline measurements will be used as covariates in the analyses to increase power. Differences in outcome measures between the 2 pairs of groups, together with 95% confidence intervals, will be calculated. All data are analysed according the "intent-to-treat principle".

The primary research objective will be tested using two likelihood ratio tests for the hazard ratio's, one for the comparison to ACD and one to ACDF. In case of homogeneity of effects, a pooled effect (adjusting for interbody fusion) will be reported. Otherwise the two analyses will be reported separately. The secondary outcome continuous measures will be compared using two t-tests in the same way (or non-parametric counterparts in case of non-symmetrical or distributions with outliers), possibly after transformations of skewed distributions.

On the other hand, repeated measurements analyses of variance for the secondary outcome measures (the continuous outcome scales) will also be performed in order to compare the evolving patterns over time.

In addition, an explorative subgroup analysis is conducted to investigate whether the treatment effect varies over specific subgroups of patients (Table 4).

**Table 4 T4:** Selected prognostic variables for subgroup analysis.

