The primary concern on studies focused on AADD, is the low incidence of events. As outlined in our sample size calculation, 750 patients will need to be randomised to elucidate the dispute on prevention of AADD in disc arthroplasty studies. In addition, an extra treatment arm of anterior discectomy without fusion will be needed to justify the high costs of cages or disc prostheses. Bartels et al. have published a similar protocol on cervical disc herniation in which 3 surgical strategies are compared[42]. However, the NDI was taken as primary outcome measure. Therefore, in our opinion, the number of patients enrolled is not enough for scientific proof of possible reduced incidence of AADD after disc arthroplasty.

The NECK trial is designed to demonstrate the effectiveness and security of cervical disc prosthesis, focused on adjacent segment degeneration and functional outcome. ACDP will be randomly and blindly compared with ACD and ACDF. The only way to elucidate the dispute on AADD prevention, is a 3 arm randomised trial with large number of patients to be included. As such we will evaluate the clinical appropriateness and superiority of disc prosthesis on one hand, cervical fusion on the other hand, and compare this to discectomy without any implant.

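### Converted ACDP patients stay in the denominators for prosthesis-specific events because all data are analysed by allocation; add results by device implanted and report the conversions

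*Protocol article*

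**What the plan says.** All places are in the Protocol article.

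- **Allocation** (Randomisation procedure): "In the operating room, after induction of anaesthesia, the surgeon will open the envelope and the allocated treatment will be performed". Any conversion therefore happens after the patient has been allocated.
- **Fallback** (section (C), ACDP): "Whenever, for surgical-technical reasons, it is not possible to implant the disc prosthesis, an interbody fusion will be performed". The next step is: "Whenever this is impossible as well, only discectomy will be performed". No expected frequency is given.
- **Analysis rule** (Data Analysis): "All data are analysed according the 'intent-to-treat principle". No exception is stated, and the article mentions no set defined by treatment received.
- **Outcomes tied to the device** (Radiographic evaluation): "we will also evaluate the cervical curvature, segmental motion, displacement or migration of the implant, and heterotopic ossification using the classification of McAfee". Under Complications: "Surgeons will also document perioperative complications like cerebrospinal fluid leakage, vascular injury, nerve root damage, and malposition of the implant".
- **Aim** (Discussion): "The NECK trial is designed to demonstrate the effectiveness and security of cervical disc prosthesis".
- **Record of surgery** (Intervention): the surgeon's findings go on a standardised CRF that is returned to the data center, so the device actually implanted should be recoverable.

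**The concern.** The fallback and the analysis rule are each reasonable alone. Together they create a mismatch for a small group of outcomes that exist only if a particular device is in the neck. A patient allocated to ACDP who receives a cage, or nothing, cannot have a migrated prosthesis or ossification around one, yet is counted among those who could. If the cage of a converted patient moves, that event appears under ACDP.

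What is at stake is how the prosthesis safety results are read. The Discussion names the security of the prosthesis as something the trial will show. A reader will take an ACDP migration or ossification rate as the risk after receiving the device, but the stated rule gives the risk after being allocated to it. For prosthesis-specific events, padding the denominator makes the device look safer, so intention to treat is not the cautious choice for these items. The article also does not say that conversions will be counted, so a reader could not undo the dilution.

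**Working it through.** **Step 1. The plan's own figures.** The Sample size section assumes annual rates of 2% (ACDP) and 7% (ACDF). The hazard ratio is ln(1 − 0.02) / ln(1 − 0.07) = 0.278, which matches the stated 0.28. The total is 1.5 × 450 = 675, and 675 / (1 − 0.10) = 750, as stated. With three equal arms, ACDP has 750 / 3 = 250 patients.

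**Step 2. Prosthesis-specific events.** Let p be the rate among patients who have a prosthesis and f the share of the ACDP arm converted. If converted patients contribute no such event,

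rate by allocation = (1 − f) × p.

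The documents give neither f nor p. Below, f runs from 2% to 20% and p = 20%; both are assumptions for illustration.

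| f (assumed) | Converted of 250 | p = 20% reads |
|---|---|---|
| 2% | 5 | 0.98 × 20% = 19.6% |
| 5% | 12.5 | 0.95 × 20% = 19.0% |
| 10% | 25 | 0.90 × 20% = 18.0% |
| 20% | 50 | 0.80 × 20% = 16.0% |

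The relative understatement equals f, whatever p is.

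**Step 3. Events of any implant.** If the outcome is counted for any implant, and q is the event rate in converted patients, the ACDP figure is (1 − f) × p + f × q. It then mixes two devices, and lies below or above p according to whether q is smaller or larger than p. This is a different distortion from the one in step 2, and the two should not be added into one statement about harm.

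**Step 4. Segmental motion.** By the same formula, an assumed mean of 8 degrees with a prosthesis and 0 degrees after fusion reads 7.2 degrees at f = 10% and 6.4 degrees at f = 20%. As a comparison of surgical strategies that is a valid result; as a description of the device it is attenuated.

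**Step 5. Does the primary comparison suffer?** Suppose every converted patient carries the 7% fusion rate. The ACDP rate is then r = (1 − f) × 2% + f × 7%, and HR = ln(1 − r) / ln(0.93). Power is taken at the planned maximum of 45 events, with a two-sided 0.05 test (the article does not state sidedness) and no allowance for the interim looks:

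- Schoenfeld: Φ(√45 / 2 × |ln HR| − 1.96)
- Freedman: Φ(√45 × (1 − HR) / (1 + HR) − 1.96)

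| f (assumed) | r | HR | Schoenfeld | Freedman |
|---|---|---|---|---|
| 0% | 2.00% | 0.278 | 99.0% | 96.6% |
| 2% | 2.10% | 0.292 | 98.5% | 95.7% |
| 5% | 2.25% | 0.314 | 97.3% | 93.9% |
| 10% | 2.50% | 0.349 | 94.2% | 89.9% |
| 20% | 3.00% | 0.420 | 82.9% | 78.3% |

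Up to about 10% conversion, power stays near or above the required 90%. It falls clearly below only towards 20%.

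**The case against.** **Intention to treat is right, and analysis by treatment received does damage.** This stands for every comparison between arms. Converted patients are selected after randomisation by surgical difficulty. Moving them out of ACDP would break the randomised comparison and could flatter the prosthesis. A reader might infer that motion and re-operations should be switched to the procedure received. The documents do not support that: the Background gives motion preservation as the main rationale of the device, and re-operation is listed as an outcome measure, so both bear on effectiveness.

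**The direction is not uniform.** This also stands. A reader might infer that prosthesis harm in general is understated. Most listed complications, such as infection, haematoma, dysphagia and nerve root damage, belong to the operation and can occur with any implant or none. Difficult converted operations could raise the ACDP rate, and cage events booked under ACDP push it up too. Harm from a failed attempt already stays with ACDP under intention to treat; a plain analysis by device received would lose it.

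**Conversions may be rare.** This is likely. Table 1 excludes immobile, fused, very narrow, kyphotic and hypermobile index levels, and the surgeons are described as experienced in all three techniques. At f = 2%, 20% reads 19.6%.

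**Safety sets belong in the analysis plan, which is not shown.** This stands in part. Had the article been silent, there would be no point to raise. It instead states a rule for all data, and an analysis plan that added results by device would have to depart from that wording. The sentence can be read as governing only between-arm comparisons, but it does not say so.

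**Conclusion.** The point holds within narrow limits. As written, patients without a prosthesis enter the ACDP denominators for prosthesis malposition, displacement or migration and heterotopic ossification, and cage events in converted patients count under ACDP. The prosthesis-specific rates are understated by the factor (1 − f): 2% to 20% in relative terms if f is 2% to 20%. That range is an assumption, and the eligibility criteria suggest its lower part. The factor also assumes that converted patients contribute no such event. That is least secure for malposition, because malposition during an abandoned attempt is itself a prosthesis event.

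A reader might also infer a threat to the primary result or the sample size. The arithmetic does not support that at low f, and the effect of allocation, fallback included, is what the superiority question should measure. This is an inexpensive improvement to the reporting of a few device outcomes.

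**What to change.** Keep intention to treat for all between-arm comparisons: the primary outcome, clinical outcomes, costs, re-operations, general complications and segmental motion. Add to Data Analysis:

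> *Implant malposition, displacement or migration and heterotopic ossification are in addition reported by the device actually implanted, as recorded on the surgical CRF, with segmental motion by device received as a supplementary analysis. Complications of an attempted but abandoned prosthesis are attributed to the prosthesis. The number of conversions and the reasons are reported per arm.*

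The fallback rule stays unchanged; this point takes no view on it.

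The cost is three sentences and one extra set of tables. The surgical CRF already goes to the data center; check that it names the device implanted and the reason for any conversion. The groups in these tables are not strictly randomised, so the tables should be labelled descriptive and carry no between-arm tests.
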